### Data management {19}

#### Oversight and monitoring

Medical records, registration books, and special records for clinical observation, including doctors' clinical medical records, are all used in this study;All data and records relating to clinical observations are kept in the investigator or clinical trial medical facility and made directly accessible to the originator of the clinical trial or the person in charge of the competent authority;Clinical observation investigators are responsible for preserving the relevant data collected. No one, other than members of the study group, ethics committees, or medical regulators, will have access to the data collected in this study without good reason.

### Confidentiality {27}

Clinical observation investigators are responsible for preserving the relevant data collected. No one other than members of the study group, ethics committees, or medical regulators will have access to the data collected in this study without reasonable reason.

### Plans for collection, laboratory evaluation and storage of biological specimens for genetic or molecular analysis in this trial/future use {33}

Not applicable, no samples were collected.

## Statistical methods

### Statistical methods for primary and secondary outcomes {20a}

The statistical software SPSS 25.0 was used for analysis. The normality of metric data, such as ASES scores, Constant scores, VAS scores, shoulder joint mobility, AHD, surgical duration, intraoperative blood loss, and postoperative drainage volume, was assessed using the Shapiro‒Wilk test and graphical analysis. Intergroup differences in metric data conforming to a normal distribution were evaluated using independent samples *t* tests, while nonnormally distributed metric data were assessed using the Mann‒Whitney *U* test. Count variables, such as the occurrence of complications, were evaluated for intergroup differences using the chi-square test. Paired samples *t* test was employed to assess intragroup differences in normally distributed metric data before and after surgery, while nonnormally distributed metric data were represented by median (interquartile range) and assessed using the Wilcoxon rank-sum test. Comparison of ordinal data, such as Hamada classification, Warner classification, Goutallier classification, and Sugaya classification, was conducted using the Wilcoxon rank-sum test. A *p* value less than 0.05 was considered statistically significant.

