#### Primary outcome

The ASES score and the Constant-Murley shoulder score were obtained during the preoperative stage, as well as at 3 months, 6 months, 12 months and 24 months.

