### Sample size {14}

Sample size calculation for ASES score analysis was performed with an expected standard deviation (SD) of 5.8, a significance level at 5% and power of 0.90 and resulted in 25 participants in each group (50 participants with allowance for 15% drop-out).

In our previous research on postoperative ASES scores of SCR, the score was 87.6 ± 5.8 at the latest follow-up. The best ASES result published by Mihata was 93.1 ± 8.1 (Structural and clinical outcomes after superior capsule reconstruction using an at least 6-mm thick autogenous fascia latas including the intermuscular septum). With a type I error rate of 0.05 (*α* = 0.05, two-tailed) and a power of 90% (*β* = 0.10), the sample size for the study protocol was calculated as 25 patients per group based on the primary outcome indicator by PASS 2021 (Power Analysis and Sample Size, NCSS, LLC, USA). Assuming a 15% drop-out rate, we plan to recruit 58 participants (29 per group) to the study.

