### Methods for additional analyses (e.g. subgroup analyses) {20b}

No additional analyses were performed.

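### The between-group ASES and Constant comparison is valid but leaves out the preoperative score and lets a normality check choose the primary test; one pre-stated baseline-adjusted model would be a free improvement

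*Protocol article*

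**What the plan says.** All references are to the protocol article.

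- **Choice of test.** Statistical methods {20a} lists ASES and Constant among the metric data. Normality is judged on the trial data by a Shapiro-Wilk "test and graphical analysis". For data that look normal the rule is: "Intergroup differences in metric data conforming to a normal distribution were evaluated using independent samples" t tests. Otherwise the arms are compared by a Mann-Whitney U test. No covariate, change score or repeated-measures model is named for the comparison between arms.
- **Use of the preoperative score.** Under Primary outcome, "The ASES score and the Constant-Murley shoulder score were obtained during the preoperative stage" and again at 3, 6, 12 and 24 months. The only stated use of the preoperative value is within each arm: a paired t "test was employed to assess intragroup differences in normally distributed metric data before and after surgery", with a Wilcoxon test as the non-normal counterpart.
- **Other analyses.** Section {20b} says: "No additional analyses were performed".
- **Sample size {14}.** "Sample size calculation for ASES score analysis was performed with an expected standard deviation (SD) of 5.8", 90% power and two-sided 5% significance give 25 per group. The section quotes the team's own SCR result, "the score was 87.6 ± 5.8 at the latest follow-up", and a published SCR result of 93.1 ± 8.1. It does not state a target difference.
- **Primary visit.** Section {18b} puts the primary outcome at 3 months. The Primary outcome section lists every visit without choosing one.

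**The concern.** A statistical analysis plan may exist that is not shown. The article nevertheless states the between-group method outright, so the choice can be judged as written. Two things follow from it.

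First, a score measured before surgery usually explains some of the variation in the same score afterwards. Leaving it out of the between-arm comparison keeps that variation in the error term. The trial expects about 49 evaluable patients (58 × 0.85 = 49.3), so precision matters.

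Second, the two candidate tests answer different questions. The t test gives a difference in means, which is the quantity the sample size rests on. The Mann-Whitney test compares ranks and does not estimate that difference. Under the stated rule, a normality check with a graphical element decides after data collection which of the two becomes the primary result. The rule does not say what happens when one arm looks normal and the other does not, or when the visits disagree.

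**Working it through.** **Inputs.** SD 5.8, two-sided α = 0.05, power 0.90 and 25 per group come from Sample size {14}. The difference is inferred as 93.1 − 87.6 = 5.5. The correlation r between preoperative and follow-up ASES is not in the documents, so a range is shown.

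**1. The protocol's own figure.** The standard error of the difference is 5.8 × √(2/25) = 1.640, and the noncentrality is 5.5/1.640 = 3.353. With 48 degrees of freedom, power is 90.7%. At 24 per group it is 89.5%, so 25 is the smallest group size that reaches 90%. The stated figure is reproduced, and it is an unadjusted comparison of two means.

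**2. Adding the preoperative score (ANCOVA).** Residual SD = 5.8 × √(1 − r²), with 2n − 3 = 47 degrees of freedom.

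| Assumed r | Residual SD | Noncentrality | Power at 25 per arm | n per arm for 90% |
|---|---|---|---|---|
| unadjusted | 5.80 | 3.353 | 90.7% | 25 |
| 0.1 | 5.77 | 3.370 | 91.0% | 25 |
| 0.3 | 5.53 | 3.515 | 93.1% | 23 |
| 0.5 | 5.02 | 3.871 | about 97% | 19 |
| 0.6 | 4.64 | 4.191 | 98.4% | 17 |

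Put as sample size, omitting baseline costs a factor 1/(1 − r²): 1.01 at r = 0.1, 1.10 at 0.3, 1.33 at 0.5 and 1.56 at 0.6.

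**3. If the SD is larger.** Pooling the two quoted SDs gives √((5.8² + 8.1²)/2) = 7.04. Noncentrality is then 5.5/(7.04 × √(2/25)) = 2.760 and unadjusted power is 77.2%. Adjusted power is 80.9% at r = 0.3, 87.7% at 0.5 and 92.2% at 0.6.

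**4. The two-step rule.** This was simulated with 25 per arm and 6,000 trials per setting. The t test was used only if both arms passed Shapiro-Wilk at 5%. The graphical step cannot be simulated and was left out.

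| Data | t test chosen | Type I error, two-step | Power: two-step | Power: always t | Power: always Mann-Whitney |
|---|---|---|---|---|---|
| Normal, SD 5.8 | 90% | 0.051 | 90.3% | 90.4% | 88.8% |
| Left-skewed (assumed gamma shape 2, SD 5.8) | 12% | 0.053 | 95.1% | 89.6% | 95.1% |

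With perfectly normal data, about one trial in ten is still sent to the rank test by chance (1 − 0.95² = 9.75%). With clearly skewed data, about one in eight still gets the t test. The error rate hardly moves. What changes is which quantity is reported.

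**The case against.** The strongest reply is that nothing stated is invalid. An unadjusted two-sample test is sound in a 1:1 randomised trial, and chance baseline imbalance is already covered by its type I error and confidence interval. The simulation bears this out, and with skewed scores the rank test has more power than the t test. On the protocol's own inputs the power target is met without adjustment, and at r = 0.1 the gain is 0.3 percentage points. All of this stands. The point is therefore about efficiency and pre-specification, not about an error.

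Several stronger readings are tempting, and the documents do not support them:

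- *The missing covariate leaves the trial at 77% power.* That figure needs the SD of 8.1, quoted for a published SCR series. The trial is sized on 5.8, where power is 90.7%. A larger SD is a separate sample-size question; it only makes adjustment more useful.
- *A ceiling on ASES will make one arm fail Shapiro-Wilk far more often than the other.* The document does not give the scale maximum, and 93.1 ± 8.1 describes the comparator operation, not an expected STR distribution. Capping a normal distribution with those values at an assumed 100 changes it to mean 92.2 and SD 6.8, so rejection rates simulated that way do not apply to 93.1 ± 8.1. The rule also includes graphs, so such rates are not rates of test choice.
- *Different tests would be used in different arms.* A between-arm comparison uses one test for both.
- *The preoperative score is not used at all.* It is used in the paired tests; it is absent only between arms.
- *The adjusted analysis belongs at 24 months.* The article does not settle the visit.

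**Conclusion.** The point holds as a free improvement. The stated between-arm tests are valid, but they set aside a baseline measurement already in hand, and they leave the data to decide whether the primary result is a mean difference or a rank comparison.

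On SD 5.8, the inferred 5.5-point difference and 25 per arm, adjustment moves power from 90.7% to between about 91% (r = 0.1) and 98% (r = 0.6). If the SD is nearer 7, the move is from 77% to between 81% (r = 0.3) and 92% (r = 0.6). These sizes rest on an assumed correlation, on the inferred difference and on normally distributed scores. That the comparison is unadjusted and the test chosen by the data rests only on the article's text.

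**What to change.** In Statistical methods {20a}, replace the test-selection rule for the ASES and Constant between-arm comparison with one pre-stated model, used whatever the normality check shows. Either of these would do:

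- ANCOVA at the primary visit, with arm and the preoperative score; or
- a mixed model for repeated measures with arm, visit, arm by visit, and the preoperative score as covariate.

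Report the adjusted mean difference with its 95% CI at one named primary visit. Before that visit is written in, reconcile section {18b} (3 months) with the Primary outcome section (all visits, none chosen). Keep the Mann-Whitney test as a sensitivity analysis, which also covers the case of skewed scores.

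The cost is a wording change and, for ANCOVA, one degree of freedom. No new data, visits or patients are needed. The change should be made before anyone sees outcome data by arm.

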#### Other evaluation

Safety indicators: At 6 weeks, 3 months, 6 months, and 12 months following the surgical procedure, the occurrences of adverse events such as infections, fat embolism, deep vein thrombosis in the lower extremities, and retearing were documented.Isokinetic muscle strength testing and surface EMG testing were used to evaluate the improvement in shoulder abduction muscle strength during the preoperative stage, as well as at 6 months, 12 months and 24 months postoperatively.

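### The before-after comparison of non-normal data is assigned the Wilcoxon rank-sum test, which is for independent samples; the paired signed-rank test should be named

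*Protocol article*

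**What the plan says.** All the relevant text is in the protocol article, section {20a} on statistical methods for primary and secondary outcomes.

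- **Between arms, metric data.** Independent-samples t test if normal, "while nonnormally distributed metric data were assessed using the Mann‒Whitney *U* test".
- **Within an arm, before and after surgery, metric data.** If normal: "Paired samples *t* test was employed to assess intragroup differences in normally distributed metric data before and after surgery". The same sentence then gives the non-normal branch: "nonnormally distributed metric data were represented by median (interquartile range) and assessed using the Wilcoxon rank-sum test".
- **Ordinal grades.** "Comparison of ordinal data, such as Hamada classification, Warner classification, Goutallier classification, and Sugaya classification, was conducted using the Wilcoxon rank-sum test". This sentence does not say whether the comparison is between arms or over time.

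The metric variables listed there include ASES, Constant, VAS, shoulder mobility and AHD. By Outcomes {12}, imaging, VAS, shoulder motion and the two function scores are collected before surgery and at 3, 6, 12 and 24 months.

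**The concern.** A before-after comparison within one arm uses two measurements on the same patients. The rank-sum test treats them as two unrelated groups. Its null variance leaves out the covariance between the two measurements, so its p value is miscalibrated unless that correlation is zero. With positive correlation, the usual case for repeated scores on one shoulder, the test is too conservative and can miss a modest change.

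The sentence cannot be rescued as the between-arm fallback, because that role already belongs to the Mann-Whitney U test, which is the rank-sum test under another name.

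The branch could well be used. VAS (0 to 10) and ASES are bounded scales, and non-normality sends a variable to this test at each follow-up visit. An analyst who follows the text literally runs the wrong test. One who silently uses the signed-rank test departs from the published plan.

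**Working it through.** **1. Number of pairs per arm.** Sample size {14} uses an SD of 5.8, 5% two-sided alpha and 90% power. The means it cites are 87.6 and 93.1, a difference of 5.5.

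n = 2 × (1.960 + 1.282)² × 5.8² / 5.5² = 23.4, so 24 per arm by the normal approximation and 25 by the noncentral t. The stated 25 per arm reproduces. The plan recruits 29 per arm to allow for drop-out, so a within-arm comparison has about 25 to 29 pairs.

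**2. Why ignoring the pairing matters.** With common SD σ and pre-post correlation ρ:

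- true variance of the mean before-after difference: 2σ²(1 − ρ)/n
- variance assumed by an independent-samples test: 2σ²/n

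The test's cut-off of 1.96 therefore acts as 1.96/√(1 − ρ). This argument is for means; ranks behave similarly.

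| ρ (assumed) | effective cut-off | approximate two-sided type I error |
|---|---|---|
| −0.3 | 1.96/√1.3 = 1.72 | 8.6% |
| 0 | 1.96 | 5.0% |
| 0.3 | 1.96/√0.7 = 2.34 | 1.9% |
| 0.5 | 1.96/√0.5 = 2.77 | 0.6% |
| 0.7 | 1.96/√0.3 = 3.58 | below 0.1% |

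**3. Simulation of the two rank tests.** Inputs: 25 pairs, normal data, two-sided 0.05. The correlations and the sizes of change are assumptions; the document gives neither.

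| ρ | type I error, rank-sum | type I error, signed-rank | power at 0.5 SD, rank-sum | power at 0.5 SD, signed-rank |
|---|---|---|---|---|
| 0.3 | 1.9% | about 5% | 36% | 50% |
| 0.5 | 0.9% | about 5% | 35% | 65% |
| 0.7 | 0.3% | about 5% | 34% | 87% |

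A separate run of 4,000 replicates gave rank-sum type I errors of 2.1%, 0.5% and 0.2%. The smallest values carry simulation error, but the pattern does not change. With 29 pairs and ρ = 0.5, rank-sum type I error was 0.5%, and power at 0.5 SD was 44% against 73%.

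**4. Where the effect shrinks or reverses.** For a 1.0 SD change with 25 pairs and ρ from 0.3 to 0.7, power is 95% to 99% for rank-sum and 98% to 100% for signed-rank. At 1.5 SD both reach 100%. At ρ = −0.3 the rank-sum test becomes too liberal (8.1% with 25 pairs).

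**The case against.** **Small practical effect.** The trial's objective is to compare STR with SCR. The between-arm tests of ASES and Constant (independent t or Mann-Whitney) suit independent arms and are untouched. Under plausible positive correlation the error is conservative, and if surgery moves the scores by 1 SD or more, either test will detect it. The simulation also used normal data, while the branch applies only to non-normal data. All of this stands. It limits the size of the point, but a test for independent samples is still named for paired data.

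**A stronger reading that a reader might infer: chi-square is also wrong for complications.** The plan states "Count variables, such as the occurrence of complications, were evaluated for intergroup differences using the chi-square test", and the events listed are "infections, fat embolism, deep vein thrombosis in the lower extremities, and retearing were documented". With 29 per arm, fewer than 10 events in total puts expected counts below 5, and single tables can look alarming: 0 against 4 events gives p = 0.038 by Pearson chi-square and 0.112 by Fisher. The documents do not support calling this an error:

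- They give no rates for infection, embolism or thrombosis. The only one given is 21% for retear after SCR, which means 0.21 × 29 = 6.1 expected events per arm.
- Exact enumeration at 29 per arm gives Pearson a type I error of 0.03%, 2.7%, 5.3% and 4.8% at common rates of 1%, 5%, 10% and 21%. Over rates of 1% to 30%, with 25 or 29 per arm, it never exceeded 5.5%.
- The gap between the p values largely reflects Fisher's conservatism: its type I error is 0.9% at a 10% rate and 2.2% at 21%. For an illustrative 21% against 5%, a blanket switch to Fisher cuts power from 48% to 26%.
- A fallback for small expected counts is detail commonly left to an analysis plan.

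An exact test is therefore a trade-off here and not a correction.

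**Conclusion.** The point holds as a minor correction. Section {20a} names an independent-samples test for non-normal before-after data, and no reading of the sentence makes that right.

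Its size depends on assumptions outside the document. With positive pre-post correlation of 0.3 to 0.7 and 25 pairs, type I error falls from 5% to between about 2% and 0.3%. Power for a 0.5 SD change is about 35%, where the signed-rank test would have 50% to 87%. For changes of 1 SD or more little is lost.

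Two wider conclusions should not be drawn. The comparison of STR with SCR on the primary scores is not affected. Nor does the plan produce wrong p values in both directions: the rank-sum error is conservative in the plausible case, and the chi-square test does not materially inflate type I error at these arm sizes.

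**What to change.** In section {20a}:

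- For within-group before-after comparisons of non-normal metric data, replace the Wilcoxon rank-sum test by the Wilcoxon signed-rank test.
- In the sentence on ordinal grades, say which comparison is meant: the rank-sum test between arms, and the signed-rank test wherever grades are compared before and after surgery.

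The cost is one changed word and one clarified sentence, made before analysis. It needs no new data and changes neither the sample size nor the design.

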### Interim analyses {21b}

The interim analysis was performed when 50% of the randomly assigned patients reached the primary endpoint. The interim analysis was carried out by independent statisticians who were blinded to the allocation of treatment. The statisticians will report to the independent Data and Safety Monitoring Commission. The results of the interim analysis will be discussed with the Steering Committee at a joint meeting. The steering committee decided to proceed with the trial and will report to the Central Ethics Committee.

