### Procedure for unblinding if needed {17b}

Because a surgical procedure is involved, the surgeons including the principal investigator were unblinded to the trial, and the evaluators collecting outcome data did not join the operation and were blinded throughout the study. When there is serious adverse event reporting and harms or the trial is finished, it will be unblinded.

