## Oversight and monitoring

### Composition of the coordinating centre and trial steering committee {5d}

The study will be performed by the Sports Medicine Center at Southwestern Hospital. There is no other coordinating centre. The trial steering committee consisted of the ethics committee of the First Affiliated Hospital of Army Medical University (No. AKY2022126) and the clinical research team. The research team consists of two principal investigators who oversee the study and are responsible for medical responsibilities, a study coordinator who plans patient visits, and an investigator who is responsible for data management and trial management. The research team meets weekly to assess progress, identify potential test subjects and work out logistical issues. A statistician was involved in the design of the trial and consulted on statistical issues throughout the study. Study leader [name] identified the enrolled patients in the outpatient department. A researcher collected general patient information. To improve the reliability of the test and reduce the differences between operators, the following measures were taken: All the operations were led by [name], and all the operations were photographed and recorded by video. The test data were evaluated and counted by one person.

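### Results of the 50% interim analysis go to a steering committee that includes the unblinded principal investigator, and no significance level is reserved should that look allow an efficacy claim

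*Protocol article*

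**What the plan says.** All references are to the protocol article.

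- **Interim analyses {21b}.** One look is planned: "The interim analysis was performed when 50% of the randomly assigned patients reached the primary endpoint". Independent statisticians, blinded to allocation, run it and report to an independent Data and Safety Monitoring Commission. Then: "The results of the interim analysis will be discussed with the Steering Committee at a joint meeting". The Steering Committee makes the decision on continuation. The section gives no purpose for the look, no test, no threshold and no stopping rule.
- **Composition of the coordinating centre and trial steering committee {5d}.** The committee is the hospital's ethics committee ("No. AKY2022126) and the clinical research team"). The team comprises two principal investigators, a coordinator, and an investigator responsible for data and trial management.
- **Procedure for unblinding {17b}.** "the surgeons including the principal investigator were unblinded to the trial". Concealment mechanism {16b} adds that researchers open the allocation before surgery.
- **Statistical methods {20a}.** The only analysis threshold is: "A *p* value less than 0.05 was considered statistically significant".
- **Sample size {14}.** "With a type I error rate of 0.05 (*α* = 0.05, two-tailed) and a power of 90"% gives 25 per group, raised to 29 per group (58 in all) for 15% drop-out.
- **Plans to promote participant retention {18b}.** The primary outcome is placed at 3 months after the intervention.

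**The concern.** There are two separate problems.

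**Disclosure.** The plan sends interim results to a group containing at least one person who knows each patient's allocation and has a direct part in the rest of the trial. The protocol has one senior surgeon and one team perform every operation, and irreparability, which is an inclusion criterion, is judged during surgery. A tear judged repairable at that point is repaired directly, and the patient leaves the allocated procedure. A surgeon who knows both the allocation and the trend would be making that judgement for every later patient. Recruitment and follow-up are open to the same influence. The bias need not be deliberate, and it cannot be measured afterwards.

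**Error rate.** The full 5% is assigned to the final test. If a comparison at the interim could also be declared positive at p<0.05, the trial would have two chances to succeed under the null hypothesis and the stated 5% would not hold.

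**Working it through.** **1. Who sees the results.** The interim section names the Steering Committee as recipient and decision-maker. The composition section puts both principal investigators on it. The unblinding section says that the principal investigator is among the unblinded surgeons. The three statements together create the route. The statisticians' own blinding does not close it: in a single-centre trial of 58 patients, results by coded group can be matched to allocations that a committee member already knows.

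**2. When the look falls.** Inputs: 58 patients; recruitment from January 2024 to January 2026 (Trial status), so 24 months; primary time point 3 months. Even accrual is assumed.
- Rate: 58/24 = 2.42 per month.
- 50% of 58 = 29 patients, reached at 29/2.42 = 12 months, so about January 2025.
- Adding 3 months gives month 15, about April 2025.
- Enrolled by then: 15 × 2.42 ≈ 36, leaving 58 − 36 = 22 still to enter.

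**3. Does the sample size set alpha aside for a look?** Inputs: SD 5.8; two-sided alpha 0.05; power 0.90; difference 93.1 − 87.6 = 5.5. The difference is inferred from the two means quoted in the section, which does not state it as the effect size.
- Normal formula: n = 2 × (1.960 + 1.282)² × 5.8²/5.5² = 2 × 10.51 × 33.64/30.25 ≈ 23.4, so 24 per group.
- Two-sample t test (noncentral t): power 0.895 at 24 and 0.907 at 25, so 25 per group.

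The plan's 25 is reproduced as a fixed-sample t test at the full 0.05. Nothing is reserved for an interim.

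**4. Error rate if both looks could be claimed at p<0.05.** Under the null hypothesis the interim and final statistics Z1 and Z2 are approximately bivariate normal with correlation √0.5 = 0.707 at half the information.
- Overall error = 1 − P(|Z1| ≤ 1.96 and |Z2| ≤ 1.96) = 0.0831.
- Simulated t tests with 12 or 13 of 25 per group at the interim: 8.4% and 8.3%.
- Information fraction 0.4 to 0.6: 8.6% to 8.0%.

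**5. Limits that would hold 5% overall at a 50% look.**

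| Rule | Interim p | Final p |
|---|---|---|
| O'Brien-Fleming (z = 2.797, 1.977) | 0.0052 | 0.0480 |
| Pocock (z = 2.178 at both) | 0.0294 | 0.0294 |
| Haybittle-Peto | 0.001 | 0.0498 |
| No efficacy claim or efficacy stop at the interim | none | 0.05 |

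**The case against.** The strongest reply is that the interim section names no efficacy test and no efficacy stop. The 0.05 rule stands in a different section, and a boundary may be in an analysis plan that is not shown. This is right as far as alpha is concerned: a reader might infer that the plan as written inflates the type I error, but the documents support that only conditionally. A look confined to safety would inflate nothing.

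The second reply is that safeguards exist: independent blinded statisticians, an independent commission, and outcome evaluators kept blind throughout. The text also does not say outright that by-arm results are released, and the surgeons know each allocation anyway. All of this is fair, and it narrows the harm to knowledge of the trend. It does not remove it. The section says that results, not a recommendation, are discussed, and an analysis plan would not change who sits on the committee. The section headed for the monitoring committee's composition and role describes only record-keeping and data access, so it does not limit what is passed on.

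Four stronger readings are not supported:
- **The whole research team is unblinded.** Only the surgeons, including the principal investigator, and the researchers who open the allocation are described so. The coordinator and the data manager are not identified as unblinded.
- **The decision to continue is already made.** The past tense suggests this, but the article uses it for planned steps throughout, and the same sentence goes on in the future tense.
- **The error rate is far above 8.3%, because two scores at several visits would each be tested at both looks.** Any such figure needs correlations that the documents do not give. Most of it would arise at the final analysis alone, which is a separate multiplicity question.
- **The look comes too late to be useful, because the endpoint is at 24 months.** The one section that fixes a single primary time point says 3 months. A 24-month trigger would also fall after recruitment had closed, which would remove the concern about later enrolment.

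**Conclusion.** The disclosure route holds without conditions on alpha: it follows from what the interim, committee-composition and unblinding sections state. With the 3-month time point and even accrual, it would open with about 22 of 58 patients still to be enrolled; uneven accrual would change that number. The size of any resulting bias cannot be calculated.

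The alpha problem is conditional. If an interim p<0.05 can stop the trial or be claimed as efficacy, the overall two-sided error is about 8.3% (8.0% to 8.6% for information fractions 0.6 to 0.4), for one primary comparison tested twice. If it cannot, the final test keeps 5%. The protocol should say which applies. The point should be corrected, but it does not invalidate the design.

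**What to change.** Reword Interim analyses {21b} to state that:

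1. the interim is for safety and data quality only, with no between-group efficacy test, so the final test keeps two-sided 0.05;
2. any by-arm results stay within the independent Data and Safety Monitoring Commission;
3. the Steering Committee receives only the commission's recommendation: continue, modify or stop;
4. the look is triggered by one named score at one named visit.

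This costs a few sentences and no alpha, power or patients.

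If early stopping for efficacy is wanted, replace item 1 with O'Brien-Fleming limits on ASES at the named visit: p<0.0052 at the interim and p<0.0480 at the end. The cost is a slightly stricter final threshold (0.0480 instead of 0.05). The sample size section should then say that the design has two looks. Items 2 to 4 apply in either case.
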